### Randomization and masking

A design of block randomization has been applied to perform the allocation. All the enrolled patients, who meet the inclusion criteria and sign the informed consent, will be randomly assigned to the experimental group or the control group in a ratio of 1:1 after a 2-week wash-out period. The random numbers from 001 to 312 were generated by SAS 9.2 and saved by an independent researcher. The random numbers and corresponding drug codes are the unique identification code of participants. The randomization sequence will be generated in a website program (cloud.medroad.cn) by an independent researcher out of the trial team. After necessary baseline evaluation for each participant who agreed to be enrolled, randomization will be performed. The random number generated by the above website program will be given to a trial team researcher for completing the enrollment. The random sequence will be preserved within opaque, sealed envelopes by an independent researcher for allocation concealment.

All the patients, recruiters, data collectors, outcome assessors, and sponsors will be all blind to the treatment allocation and what each intervention envelope included in the whole process of the trial. In case of emergency, the corresponding random number and treatment allocation will be identified for researchers and supervisors as soon as possible. The randomization design and random numbers are provided by the Jiangsu Famous Medical Technology Co., Ltd. in Nanjing, China.

### Procedures and interventions

Patients in the experimental group will be treated with JHG for 52 weeks, while the control group are treated with a JHG placebo. JHG is a Chinese herbal compound medicine. The compounds of one dosage for JHG are found in Table 1. The placebo used in this study will contain 5% of the same components of JHG. All the JHG and placebo will be produced and packed by Jiang Yin Tian Jiang Pharmaceutical Co. Ltd., Jiangsu, People’s Republic of China, without any difference in the appearance, color, smell, and weight. The drug quality will be tested by the organization with specific qualifications before application and consistent with the required quality standards. Each dosage of JHG granules or placebo has been produced and packed into 4 bags with 10.9 g per bag (Batch number: 2006337). JHG or JHG placebo will be prescribed 2 bags each time, twice a day orally with 5 days on and 2 days off.

**Table 1 Tab1:** Components of Jin-shui Huan-xian granules

Chinese name	Latin name	Parts of the substances	Amount (g)
Ren Shen	*Radix Ginseng*	Root	6
Shu Di Huang	*Rehm,annia glutinosa Libosch*	Root tuber	12
Mai Dong	*Ophiopogon japonicus*	Root tuber	9
Gua Lou	*Trichosanthes kirilowii Maxim*	Mature fruit	9
Zhe Bei Mu	*Fritillaria thunbergii Miq*	Bulb	9
Mu Dan Pi	*Paeonia Suffruticosa Andrew*	Root bark	9
Zhi Yin Yang Huo	*Epimedium brevicornu Maxim*	Whole herb	6
Chao Bai Guo	*Ginkgo biloba L*	Mature seed	9
Chen Pi	*Citrus reticulata Blanco*	Peel of fruit	9
Zhi Gan Cao	*Glycyrrhiza uralensis Fisch*	Root and rhizome	9

At the same time, all the patients will also be treated with conventional modern medicine. Considering the side effects and costs, the application of pirfenidone and nintedanib will not be limited uniformly. During the whole procedure, all the patients will be visited every 13 weeks and receive given physical examinations. Blood and urine samples and exhaled breath condensate will be collected with the participants’ consent for further researches. If patients are under AE, the Chinese medicine granule or placebo will be suspended until the condition becomes stable. To improve the patients’ adherence, the remaining drugs and empty bags will also be returned except for regular telephone follow-up. The whole procedure for each patient is found in Fig. 2.

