## Introduction

Idiopathic pulmonary fibrosis (IPF) is a progressive interstitial lung disease with poor prognosis and short median survival [1]. The etiology remains not completely clear [2]. With a low prevalence rate, some scholars consider it as a rare disease [3]. In China, it has also been included in the list of rare diseases in 2018. However, different studies show that it has been more common in recent years [4, 5]. After diagnosis, IPF patients will follow a median survival of 2–5 years [5]. Data also shows that IPF patients in Sweden will spend an annual average of $13,975 for hospitalization [6]. In America, a total of 2 billion dollars has been spent on the prevention and treatment of IPF every year [7]. IPF has caused a heavy socio-economic burden.

Although different studies have been performed in recent years, the available treatments remain limited. As reported in the latest international guidelines for IPF, only pirfenidone and nintedanib are recommended in clinical application [8]. They could improve pulmonary function, quality of life, and exercise capacity and delay the disease progression for IPF patients [9–11]. However, the related side effects have also been reported. One study showed that a total of more than 10% of IPF patients taking pirfenidone or nintedanib have discontinued medication permanently due to side effects [12], and their long-term effects are still under debate. Up to now, evidences for other drugs are still insufficient [13–20]. Limited researches have also been performed on non-drug treatment for IPF [21]. However, the levels of the available evidences are also low. It is urgent to conduct further researches on the treatments of IPF [22].

Traditional Chinese medicine (TCM) has different treatments and certain efficacy for respiratory diseases. Chinese herbal medicine (CHM) is the most used measures. According to TCM theory and our previous studies, IPF should be treated according to *feiwei* or *feibi*, and the core TCM pathogenesis includes vital *qi* deficiency, lung collaterals obstruction, phlegm and blood stasis, and accumulation of damage. We have also developed a TCM therapeutic scheme for IPF based on the above studies. Then, the CHM formulation has been optimized to Jin-shui Huan-xian granule (JHG) by clinical application and basic experiments.

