### Sample size

The calculation formula (*n* = (*u*_*α*_ + *u*_*β*_)^2^(1 + 1/*k*)*σ*^2^/*δ*^2^) based on the comparison of the means of two independent samples has been adopted to calculate the target sample size. *N* and *k***n* represent the target sample size of the experimental and control groups, respectively. The total variance (*σ*^2^) will be represented by the sample variance (*s*^2^). The formulas *s*^2^ = (*s*_*e*_^2^ + *ks*_*c*_^2^)/(1 + *k*) and *δ* = |‾*x*_*e*_ − ‾*x*_*c*_| have also been adopted. ‾*x*_*e*_ and ‾*x*_*c*_ represent the means of the experimental and control groups, while *s*_*e*_ and *s*_*c*_ represent the standard deviation (SD), respectively. Two-tailed values of *α* and *β* are 0.05 and 0.01, respectively. The ratio of the experimental and control group samples in this trial is 1:1, so the *k* value is 1.

Based on our previous clinical trial (to be published), the frequencies of AEs and 6-min walking distance (6MWD) have been set up as the primary outcomes in this trial. There was a significant difference between the two groups in our previous study for AE. So, the calculation of sample size in this study will refer to 6MWD.

For 6MWD, the mean was 374.38 m in the experimental group and 342.57 m in the control group. The SD was 87.67 m in the experimental group and 81.18 in the control group. The target sample size in each group was 124. Taking a drop-out rate of 20%, the target sample size is 156 in each group, and the total target sample size is 312.

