### Outcome measures

Assessment will be performed by outcome measures at baseline, end of treatment, and given follow-up points. The primary outcomes include frequencies of AEIPF, 6-min walking distance (6MWD), and the proportion of patients with disease progression-free. The secondary outcomes include pulmonary function, all-cause mortality, clinical symptom and signs, dyspnea, and health-related quality of life (HRQoL).

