##### Proportion of disease progression-free survivals

The endpoints of free disease progression in this study include any of the following events [29]: forced vital capacity (FVC) decreased by 10%, diffusing capacity percentage of the predicted value (DLCO%) by 15% compared to baseline, patient death, and lung transplantation. At the end of treatment, the proportion of the patients without any of the above endpoints will be calculated.

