##### Data management and statistical analysis plan

Statistical analysis will be conducted both in the intent-to-treat (ITT) and pre-protocol (PP) data. ITT analysis will be applied to analyze the safety data. All the data from any included patients will be analyzed regardless of their withdrawal from the trial. The PP analysis will be adopted to assess the efficacy of the interventions. If data permit, sub-group analysis will also be performed to help clarify the therapeutic effect of interventions.

All the *P* values will be set as two-tailed with a significant level of 0.05. Measurement data will be shown with mean ± SD, median, and inter-quartile range. Count data will be presented by frequency or composition ratio. Analysis of variance (ANOVA) will be used to test for the differences in continuous variables, with the chi-square test for categorical variables. If necessary, the paired *t*-test will be applied to intra-group comparison data with normal distribution and homogeneous variance, and the Wilcoxon signed-rank sum test will be used for non-normal distribution or uneven variance. Repeated-measures ANOVA will be used to test the continuous response variables that are measured at more than two time points for the same patient, such as 6MWT, clinical symptoms and signs, mMRC, and HRQoL. To improve the quality of data, all the data management and statistical analysis will be conducted by the Jiangsu Famous Medical Technology Co., Ltd. in Nanjing, China.

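### Antifibrotic use, which the protocol credits with effects on two of the three primary outcomes, enters neither the described allocation nor the named tests; adjust for baseline use and base efficacy on ITT

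*Protocol article*

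**What the plan says.** Four parts of the protocol article bear on this.

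- Procedures and interventions: all patients receive conventional treatment, and "Considering the side effects and costs, the application of pirfenidone and nintedanib will not be limited uniformly".
- Introduction, on the same two drugs: "They could improve pulmonary function, quality of life, and exercise capacity and delay the disease progression for IPF patients".
- Outcome measures: "The primary outcomes include frequencies of AEIPF, 6-min walking distance (6MWD), and the proportion of patients with disease progression-free". Progression is defined by "forced vital capacity (FVC) decreased by 10%, diffusing capacity percentage of the predicted value (DLCO%) by 15% compared to baseline", death or lung transplantation, and is summarised as a proportion at the end of treatment. Pulmonary function and quality of life are secondary.
- Randomization and masking: "A design of block randomization has been applied to perform the allocation". The ratio, software, website and envelopes are described; no stratification factor is named.

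The analysis section states: "Analysis of variance (ANOVA) will be used to test for the differences in continuous variables, with the chi-square test for categorical variables". For 6MWD and other repeatedly measured outcomes it adds: "Repeated-measures ANOVA will be used to test the continuous response variables that are measured at more than two time points for the same patient". No covariate is named. Subgroup analysis is conditional on the data, with no factor given. The section opens by saying that both ITT and per-protocol data will be analysed. It then assigns ITT to safety and per-protocol to efficacy.

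**The concern.** By the protocol's own account, pirfenidone and nintedanib act on exercise capacity, lung function and progression. Their use may vary between patients, and nothing in the article links that use to the allocation or to the efficacy comparison. Two things follow.

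First, a known prognostic factor is left in the residual variation. Any chance imbalance between arms goes straight into the estimated difference in 6MWD or in the progression-free proportion.

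Second, the usual reassurance that randomisation balances such factors on average applies to everyone randomised. The per-protocol set drops patients whose adherence falls outside 80% to 120%, who take a prohibited drug, or who stop the study drug themselves. The protocol expects up to 20% to be withdrawn. If those exclusions relate to antifibrotic use differently in the two arms, the imbalance is no longer purely chance, and the unadjusted tests do nothing about it.

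**Working it through.** **Inputs from the article (Sample size).** 6MWD means are 374.38 and 342.57 m, a difference of 31.81 m. SDs are 87.67 and 81.18 m, so the pooled SD is √((87.67² + 81.18²)/2) = 84.49 m. The plan has 124 per arm before and 156 after allowance for 20% dropout (124/0.80 = 155, so the dropout step agrees to within one patient). The 124 itself does not follow from the printed inputs: two-sided α = 0.05 and β = 0.01 give 260 per arm. That is a separate matter, and nothing below depends on it. Here 124 and 156 serve only as the planned group sizes.

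**Assumptions.** The article gives neither the share of patients on antifibrotics nor the size of their effect on 6MWD. I take use p from 10% to 50% and an effect e of 15, 30 or 45 m.

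**Step 1: chance imbalance in baseline use.** SE = √(2p(1−p)/n). At n = 156 this is √(2 × 0.3 × 0.7/156) = 0.052 for p = 0.3, and 0.057 for p = 0.5.

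| n per arm | p | 95% range of imbalance (points) | P(imbalance of 10 points or more) |
|---|---|---|---|
| 156 | 0.1 | ±6.7 | 0.3% |
| 156 | 0.3 | ±10.2 | 5.4% |
| 156 | 0.5 | ±11.1 | 7.7% |
| 124 | 0.1 | ±7.5 | 0.9% |
| 124 | 0.3 | ±11.4 | 8.6% |
| 124 | 0.5 | ±12.4 | 11.5% |

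**Step 2: effect on the 6MWD difference.** Shift = imbalance × e. For 10 points this is 0.10 × 15, 30 or 45 = 1.5, 3.0 or 4.5 m, which is 4.7%, 9.4% or 14.1% of 31.81 m.

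**Step 3: precision recovered by adjustment.** The variance share explained is R² = p(1−p)e²/SD². For p = 0.3 and e = 30 m, R² = 0.21 × 900/84.49² = 0.026. Recomputing power at 124 per arm with SD × √(1−R²), for p from 0.2 to 0.5 and e from 15 to 45 m, raises it from 84.2% to between 84.4% and 86.8%.

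**Step 4: a non-chance difference.** Suppose, purely as an illustration, that selection into the per-protocol set leaves a systematic 20-point difference in use. The shift is 0.20 × 15 to 45 = 3 to 9 m, or 9% to 28% of 31.81 m. The SE of the 6MWD difference at 124 per arm is 84.49 × √(2/124) = 10.73 m. A shift of 3 to 9 m is therefore 0.28 to 0.84 SE, and two-sided rejection with no JHG effect rises from 5% to between 5.9% and 13.4%. Nothing in the article says that a difference of this size will occur.

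**The case against.** The strongest reply is that the article condenses a fuller protocol, and that an analysis plan may add covariates and name subgroups. That is fair for subgroup factors and data-collection fields, whose absence is not held against the plan here. It carries less weight for the tests, because the article commits to ANOVA and chi-square, and a chi-square test cannot hold a covariate.

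A second reply also stands. Under 1:1 randomisation, baseline use is balanced in expectation, and an unadjusted test keeps its type I error because chance imbalance is already part of sampling error. A reader might infer that the planned comparison is biased by open antifibrotic use. For a full ITT comparison the article does not support that; the loss is in precision, and Step 3 shows that it is small.

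Three further inferences go too far.

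- That all three primary outcomes are affected: the Introduction does not say that antifibrotics reduce acute exacerbations.
- That dilution by later antifibrotic starts could never be shown: the article nowhere says that use goes unrecorded.
- That a baseline covariate would correct for starts after randomisation: it cannot, and in an ITT comparison those starts are part of the effect being estimated.

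**Conclusion.** The point holds in limited form. The protocol states that two background drugs act on 6MWD and progression, leaves their use open, and names neither a stratification factor nor a covariate. For all randomised patients, the consequence is a small loss of precision and an uncorrected chance imbalance: roughly 1.5 to 4.5 m on 6MWD for a 10-point imbalance, and a power gain from adjustment of at most 2.6 points (86.8% − 84.2%). The stronger reason to act is that efficacy is assigned to the per-protocol set, where randomisation no longer guarantees balance. Step 4 shows how far a larger difference could matter, but only as a what-if. All sizes rest on assumed usage rates and assumed effects on 6MWD. The textual finding rests on no assumption.

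**What to change.** Leave background treatment policy unchanged, and amend the analysis as follows.

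1. Include baseline antifibrotic use (yes/no) as a prespecified covariate in each primary analysis: a linear or mixed model for 6MWD, a count model for exacerbations, and logistic regression for the progression-free proportion.
2. Make ITT, regardless of later antifibrotic starts, the primary efficacy analysis in place of per-protocol.
3. Name baseline use as a subgroup factor.
4. Report antifibrotic starts and stops by arm descriptively. Do not adjust for them, because they occur after randomisation.

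Covariate adjustment remains fully available although 70 patients were already enrolled when the article was submitted; stratification could now cover only later allocations.

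The cost is one degree of freedom per model and, if use is not already captured, one case report form item. Moving efficacy from per-protocol to ITT is a real change of analysis population and may make the estimated effect somewhat smaller. The sample size does not change on account of this point.

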**Fig. 2 Fig2:**
[figure not shown]
Research flow chart for every participants in the study

### Outcome measures

Assessment will be performed by outcome measures at baseline, end of treatment, and given follow-up points. The primary outcomes include frequencies of AEIPF, 6-min walking distance (6MWD), and the proportion of patients with disease progression-free. The secondary outcomes include pulmonary function, all-cause mortality, clinical symptom and signs, dyspnea, and health-related quality of life (HRQoL).

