#### Primary outcomes

##### Exacerbations of IPF

The frequencies of acute exacerbations of IPF, which is assessed by AEIPF-related hospitalization, is the primary outcome measure. AEIPF is characterized by significant respiratory deterioration, with an unknown cause within the past 1 month [28]. If the interval between any two AEIPF-related hospitalizations is less than 7 days, they are considered as one AE. The AE will be recorded at every visit, and the total number in the whole process (1-year treatment period) will be calculated. A higher number in a given period indicate the deterioration of IPF and a worse prognosis. A lower number in the experimental group will indicate better efficacy.

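### The protocol names two primary outcomes in one section and three in another, applies 0.05 to every test, and gives no rule for what counts as success

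*Protocol article*

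**What the plan says.** All references are to the protocol article.

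- **Outcome measures** lists three primaries: "The primary outcomes include frequencies of AEIPF, 6-min walking distance (6MWD), and the proportion of patients with disease progression-free". The subsections under the heading Primary outcomes then describe each of the three.
- **Sample size** lists two: "the frequencies of AEs and 6-min walking distance (6MWD) have been set up as the primary outcomes in this trial". It does not mention the progression-free proportion. It sizes the trial on one outcome only: "So, the calculation of sample size in this study will refer to 6MWD".
- **Data management and statistical analysis plan** sets one level for all tests: "All the *P* values will be set as two-tailed with a significant level of 0.05". It gives no division of alpha, no order of testing and no statement of how many primaries must be significant.

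The Introduction and Discussion present the trial as confirming efficacy after an exploratory trial.

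**The concern.** A confirmatory trial needs one defined set of primary outcomes and one rule that turns their results into a conclusion. Here the set differs between two sections and the rule is absent.

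The status of the progression-free proportion is what is at stake. If any one success is enough, counting it as primary gives one more chance to succeed. If all must succeed, leaving it out removes a hurdle. Each choice can cite the protocol, so it could be made after the results are known. The unadjusted 0.05 adds to this, because under an any-one rule the overall false-positive rate exceeds 5% with either set.

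**Working it through.** **1. The primary set**

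| Section | Exacerbations | 6MWD | Progression-free proportion |
|---|---|---|---|
| Sample size | primary | primary | not named |
| Outcome measures and its Primary outcomes subsections | primary | primary | primary |

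The conflict is two against three, and the third outcome is the one in dispute.

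**2. The plan's own figure.** The article states no family-wise error rate, so the only figure to reproduce is 124 evaluable patients per group for 6MWD. The Sample size section gives means of 374.38 and 342.57 m (difference 31.81 m), SDs of 87.67 and 81.18 m, and 1:1 allocation. It also states "Two-tailed values of *α* and *β* are 0.05 and 0.01, respectively".

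- Variance: (87.67² + 81.18²)/2 = 7138.1, so SD = 84.49.
- n = 2 × (1.960 + 2.326)² × 7138.1 / 31.81² = 259.2, that is 260 per group.

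The stated 124 does not follow from a beta of 0.01. That is a separate problem and does not affect the error rates below. It does mean that the power figures in step 5 are recalculated at 124 per group and are not the plan's nominal 99%.

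**3. Family-wise error if any one success counts.** Assume no true effect on any primary, each tested at two-sided 0.05, with independent tests.

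- Two primaries: 1 − 0.95² = 9.75%. Bound under any dependence: 2 × 0.05 = 10%.
- Three primaries: 1 − 0.95³ = 14.26%. Bound: 3 × 0.05 = 15%.
- Three primaries, counting only false results that favour JHG: 1 − 0.975³ = 7.3%.

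The three outcomes are likely to be positively correlated, but the article gives no correlation, so a range is assumed. Simulating equally correlated two-sided z-tests (2 million draws) gives:

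| Correlation | Two primaries | Three primaries |
|---|---|---|
| 0 | 9.75% | 14.3% |
| 0.3 | 9.5% | 13.6% |
| 0.5 | 9.0% | 12.5% |
| 0.8 | 7.8% | 9.8% |

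**4. Error if all must succeed.** The chance that every test is falsely significant cannot exceed that of any one of them, so it is at most 5%. Joint power likewise cannot exceed the lowest single power.

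**5. What a rule costs on 6MWD.** With 124 evaluable per group, the standardised difference is 31.81 / (84.49 × √(2/124)) = 2.965.

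- Full 0.05 (single primary, or first in a fixed sequence): Φ(2.965 − 1.960) = 84.2%.
- Bonferroni over two (0.025): Φ(2.965 − 2.241) = 76.5%.
- Bonferroni over three (0.0167): Φ(2.965 − 2.394) = 71.6%. Family-wise error under independence is then 1 − (1 − 0.0167)³ = 4.9%.

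The same calculation is not possible for the other two outcomes, because the article gives no assumptions for them.

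**The case against.** **The rule may sit elsewhere.** This is a journal article, and testing order and alpha allocation are commonly left to the SAP or full protocol. A general 0.05 convention does not exclude an adjustment; a fixed sequence or an all-must-succeed rule also tests each outcome at 0.05. This stands in part: the missing multiplicity detail alone would not be a finding. But which outcomes are primary is protocol content, and the article contradicts itself on it. Any rule in a SAP needs one defined set to act on, and an alpha split would contradict the statistical section as written.

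**A reader might infer a third definition, with a single primary.** The exacerbations subsection says that exacerbation frequency, "which is assessed by AEIPF-related hospitalization, is the primary outcome measure". The article does not support that reading. The sentence stands under a plural heading that also covers 6MWD and the progression-free proportion, directly after all three are listed. It is most naturally loose grammar.

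**A reader might infer that any one significant result is enough, so that the trial's error rate is 14%.** No section says so. The hypothesis in Anticipated results and at the end of the Discussion joins several benefits together, which fits an any-one rule no better than an all-must-succeed rule. The 14.26% is therefore conditional on an any-one rule. It is also the independence value and not an upper limit.

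**Conclusion.** The contradiction between two and three primaries is established from the text and must be reconciled. It leaves the status of the progression-free proportion open to choice after the results, whichever success rule is meant.

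The size of the error problem depends on that unstated rule. With any-one success and no true effects, it is 9.75% or 14.26% under independence, less with positive correlation, and roughly half the three-outcome figure if only errors in JHG's favour matter. With all-must-succeed, there is no inflation. The article does not establish an actual error rate of 14%; it leaves the rate undetermined.

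**What to change.** While the trial is still blinded:

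1. Make the set of primary outcomes identical in the Sample size section, the Outcome measures section and the exacerbations subsection. Keep the third outcome, if retained, as the proportion at end of treatment that the article defines.
2. For the primaries, replace the blanket 0.05 with one stated success rule that controls the family-wise error at two-sided 0.05. Defensible options are:
   - a single primary, with the others secondary;
   - co-primaries that must all succeed;
   - an alpha split;
   - a fixed sequence in an order that the sponsor justifies.

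As one example, a sequence starting with 6MWD, the only outcome sized, keeps about 84% power for it at 124 per group, against about 72% with Bonferroni over three. Outcomes after the first non-significant one are then descriptive. Being the outcome that was sized does not by itself settle clinical priority, and another order could be justified.

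The cost is a protocol amendment with matching SAP text, and no extra patients. Depending on the rule, some power is lost or some outcomes may not be claimable. The Trial status section reports 70 patients enrolled with recruitment in progress, and the Data Availability section reports no datasets generated or analysed. At that stage the choice could still be made credibly; after unblinding it could not.
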